### Catheter ablation

Patients randomized to the hybrid treatment arm will be admitted for a staged catheter ablation treatment 3 months after the CryoMaze procedure. In general, patients will continue with warfarin or stop one of the novel anticoagulation drugs 24–48 hours before the planned procedure (unless the surgeon decides otherwise). Electro-anatomical mapping of the left and right atria will be performed using a CARTO navigation system. First, an anatomical map will be created to provide a first look at the actual locations of the CryoMaze ablation lines (regions with voltage <0.1 mV). Pulmonary vein isolation will be confirmed by the absence of signals recorded using a multielectrode circular catheter. Completeness of all linear lesions created during the surgical CryoMaze will be confirmed by a bidirectional conduction block across the relevant line. Any gaps will be re-ablated using radiofrequency catheter ablation. If the patient is in atrial tachycardia at the beginning of the procedure, the tachycardia will be mapped and ablated as the first step. If the patient is in AF, an external electrical cardioversion will be performed during the procedure to restore sinus rhythm. The investigator can then add any of the current ablation methods including substrate modification or ablation of triggers induced by an isoproterenol infusion. Inducibility of AF or atrial tachycardia at the end of the procedure will be recorded. Patients will be discharged on their current antiarrhythmic medication for the 3-month blanking period with the aim of discontinuing the medication at the first follow-up visit. Any atrial tachyarrhythmias that may occur during the blanking period after the catheter ablation may require a change of the antiarrhythmic medication or external cardioversion. Intravenous heparin will be administered during the procedure, and warfarin will continue post-operatively with a target international normalized ratio between 2.0 and 3.0. Alternatively, novel oral anticoagulants, such as dabigatran, apixaban, or rivaroxaban, will be prescribed for a period of at least 3 months.

### Follow-up

Clinical follow-up will be performed at 3, 6, 12, 18, and 24 months after the index procedure (surgical ablation in the surgical cryoablation group and catheter ablation in the hybrid group). Seven-day Holter monitoring will be performed before each follow-up in all patients. The absence or presence of atrial tachyarrhythmias on the ECG Holter will be assessed, and any need for additional ablation procedures, antiarrhythmic drugs, or cardioversions after the blanking period will be considered as a failure. Clinical status, medication, blood pressure, 12-lead electrocardiogram, and any adverse events will be documented during every visit. Unless necessary, antiarrhythmic drug therapy will be discontinued at the first follow-up visit. Medical records will be reviewed at each visit to determine the moment of antiarrhythmic medication changes.

An echocardiogram will be performed within 1 week following the surgical ablation or, if performed, within 1 week after the catheter ablation. Further echocardiograms will be performed at the 12 and 24 month follow-ups. Left atrial size will be determined using the long-axis parasternal view and the apical two-chamber view. In addition, the left ventricular end systolic and the left ventricular end diastolic diameter will be measured, and diastolic function will be assessed by computing the ratio of early to late diastolic filling, the E/A ratio.

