## Methods

The Sequential Hybrid Surgical CryoMaze Ablation versus Surgical CryoMaze Alone for the Treatment of Atrial Fibrillation (SurHyb) study was designed to be a prospective, randomized multicenter study. Patients will be recruited from three major cardiovascular centers in the Czech Republic (South Bohemia Cardiac Centre in Budweis, the Institute for Clinical and Experimental Medicine in Prague, and Na Homolce Hospital in Prague). Patients will be approached during the clinical review before the surgical operation and will be offered an opportunity to participate in the study. There will be a follow-up period of 2 years for each enrolled patient. The objective of the study is to compare a staged hybrid surgical cryoablation, followed 3 months later by catheter ablation, to a surgical CryoMaze alone. A flowchart of the SurHyb trial is shown in Fig. 1. Written informed consent will be obtained from all patients prior to the study. All participating centers will have an appointed local investigator who will be responsible for appropriate inclusion and follow-up of patients. The trial sponsor is the South Bohemia University in Budweis. The regulations regarding medical confidentiality and data protection are fulfilled.

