### Randomization

The SurHyb study is a prospective, randomized, multicenter study. After providing informed consent, patients will be randomly assigned using a computer system to one of the two groups — the hybrid group or the surgery alone group — initially in a 1:1 ratio. The surgeon will be blinded as to the treatment group until the surgery is completed. All patient data will be collected using a standard form and transmitted to a central database.

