### Primary outcome measure

The primary outcome measure is arrhythmia-free survival without class I or III antiarrhythmic drugs, which will be evaluated using a 7-day Holter monitoring at 24 months. After a 3-month blanking period, if a patient requires a repeat ablation, cardioversion, or antiarrhythmic drugs, this will be considered as a failure.

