### Statistical methods

Absolute values of continuous variables will be expressed using standard summary statistics, arithmetic mean, standard deviation, and corresponding 95 % confidence interval. The study is designed to compare recurrence rates of AF or atrial tachycardia episodes at 24 months between two treatment groups as the primary endpoint. The arrhythmia-free survival rate is defined as the percentage of patients free of atrial arrhythmias. Fisher’s exact test will be used for this categorical data to assess the difference in frequency of arrhythmia recurrence. The odds ratio and its 95 % confidence interval will be estimated as a quantitative measure of risk in the association frequency table. Differences in continuous data describing duration of arrhythmia recurrences will be tested using Student’s *t* test. Kaplan-Meier curves will be plotted to compare event-free survival time between both groups. The log-rank test will be performed to compare arrhythmia-free survival time distributions between the study arms. Influence of mutually independent risk factors will be quantified on the basis of the hazard ratio (HR) and its 95 % confidence interval. Both univariate and multivariate adjusted HRs will be estimated using the Cox proportional hazard models with an adopted forward stepwise algorithm. All variables will be analyzed on the basis of the intention-to-treat protocol. A *P* value less than 0.05 will be considered as a boundary of statistical significance of differences in all performed tests. Analyses will be performed using SPSS version 16.0 (SPSS Inc., Chicago, IL, USA).

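### The arms are followed and scored on different clocks: from surgery in control, but from catheter ablation about 3 months later in hybrid, after a second blanking period

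*Protocol article*

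**What the plan says.** All references are to the protocol article.

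- **Origin of follow-up.** Under Follow-up: "Clinical follow-up will be performed at 3, 6, 12, 18, and 24 months after the index procedure". That procedure is then defined by arm: "after the index procedure (surgical ablation in the surgical cryoablation group and catheter ablation in the hybrid group".
- **Gap between the origins.** Under Catheter ablation: "Patients randomized to the hybrid treatment arm will be admitted for a staged catheter ablation treatment 3 months after the CryoMaze procedure".
- **Randomisation.** It follows consent and precedes surgery in both arms. Under Randomization: "The surgeon will be blinded as to the treatment group until the surgery is completed".
- **Blanking.** The Surgical ablation section leaves recurrences in the first 3 months after surgery uncounted, and does not limit this to one arm. The Catheter ablation section adds, for hybrid only: "Patients will be discharged on their current antiarrhythmic medication for the 3-month blanking period".
- **Primary endpoint.** Arrhythmia-free survival off class I or III drugs, "which will be evaluated using a 7-day Holter monitoring at 24 months". Drug use, cardioversion or repeat ablation after a 3-month blanking period is a failure. The start of that period is not given there.
- **An allowance for control.** Under Surgical ablation, a control patient in persistent AF after blanking is cardioverted, and this is not a failure if sinus rhythm holds.
- **Duration and principle.** Methods: "There will be a follow-up period of 2 years for each enrolled patient". Statistical methods: "All variables will be analyzed on the basis of the intention-to-treat protocol".

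**The concern.** The arms are randomised before surgery and have the same planned care until month 3. From then on they are scored over different stretches of the postoperative course. A control patient with a new recurrence, a drug restart or a repeat ablation in month 4 or 5 has failed. A hybrid patient with a recurrence or drug change in the same months is still in blanking. The same holds for drug cover. Stopping antiarrhythmics is aimed for at the first follow-up visit, which falls at about month 3 in control and month 6 in hybrid.

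The second problem is who has a clock at all. Time zero in the hybrid arm is an event after randomisation. A hybrid patient who dies, withdraws or never has the catheter procedure has no index date, so the 24-month outcome is not defined for that patient. The comparable control patient has a date. What is at stake is whether a difference in the primary endpoint can be attributed to catheter ablation rather than to the choice of window.

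**Working it through.** **1. Timeline in months from surgery**

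| | Control | Hybrid |
|---|---|---|
| Time zero for visits | 0 | about 3 |
| Uncounted | 0–3 | 0–3 plus 3–6 |
| At risk of failure | 3–24 | 6–27 |
| Visits | 3, 6, 12, 18, 24 | 6, 9, 15, 21, 27 |
| Primary assessment | 24 | 24 + 3 = 27 |

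Both arms are at risk for 21 months, but not the same 21 months. The uncounted status of hybrid months 3–6 comes from reading two sections together: Catheter ablation names the period a blanking period, and Follow-up counts failures only after blanking.

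**2. The plan's own figure.** The Sample size calculation gives at least 130 per arm for 86% against 50–70%, with 80% power and Fisher's exact test at 5%. I take the test as two-sided, since the plan does not say. For 86% against 70%, exact Fisher power is already 80.5% at 115 per arm and is 85.5% at 130. So 130 is not reproduced exactly, but it is more than enough for the stated power. It serves below only as the number per arm.

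**3. Size of the bias if catheter ablation has no effect**

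Inputs:
- Control success S = 50–70%, from the Sample size calculation.
- n = 130 per arm, from the same section.
- k = hazard in months 3–6 divided by the hazard later. This is **assumed**; the article gives no value.

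Model: piecewise-constant hazard from surgery, the same in both arms, with later hazard h.
- Control is at risk for 3 months at kh and 18 months at h, so S = exp(−(3k + 18)h) and h = −ln(S)/(3k + 18).
- Hybrid is at risk for 21 months at h, so its success is exp(−21h).

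Example with S = 0.70 and k = 2: h = 0.3567/24 = 0.01486, and exp(−21 × 0.01486) = 0.732. The gain is 3.2 points.

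| Control success | k | Hybrid success | Spurious gain (points) | Fisher rejection |
|---|---|---|---|---|
| 70% | 1 | 70.0% | 0 | 3.7% |
| 70% | 2 | 73.2% | 3.2 | 6.7% |
| 70% | 3 | 75.8% | 5.8 | 14.8% |
| 60% | 2 | 64.0% | 4.0 | 7.8% |
| 60% | 3 | 67.2% | 7.2 | 18.7% |
| 50% | 1 | 50.0% | 0 | 4.1% |
| 50% | 2 | 54.5% | 4.5 | 9.6% |
| 50% | 3 | 58.3% | 8.3 | 24.0% |

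Against the planned difference of 86 − 70 = 16 points, a gain of 3.2 to 5.8 points is 20% to 36%. If k is below 1, then 3k + 18 is below 21 and the bias turns against hybrid.

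The model has two simplifications. It ignores the excused control cardioversion. It also lets a hybrid patient who recurs in months 3–6 start month 6 at the same hazard as everyone else. Both tend to overstate the gain.

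**4. Internal fit.** Hybrid follow-up runs about 27 months from surgery, against the 2 years stated for each enrolled patient. Intention-to-treat requires an outcome for every randomised patient, and the index-procedure clock supplies none for a hybrid patient without catheter ablation.

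**The case against.** The best defence is that the clock starts when each arm's planned treatment is complete, and that blanking after each ablation avoids scoring early postprocedural arrhythmia as failure. The control arm also has its own relief: AF persisting at month 3 can be cardioverted without penalty if sinus rhythm holds, and hybrid patients in AF are cardioverted during the catheter procedure. This stands as a partial offset. It does not cover new control recurrences, drug use or repeat ablation in months 3–6.

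The direction and size of the bias depend on a hazard shape that the article does not give. This also stands. With a constant hazard the bias is nil, and if the hazard rises late, assessing hybrid at month 27 works against it.

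Four stronger readings are tempting but not supported.
- *Every outcome is biased.* Procedure-related complications are counted for both procedures, and safety is reviewed throughout the trial. Neither is tied to the index clock.
- *Intention-to-treat is abandoned.* The article states the principle, keeps data already collected and seeks data after dropout. The gap is a missing index date for some hybrid patients.
- *Deaths before month 3 count only in control.* No section says so. Cardiovascular mortality has no stated origin, and the article does not say whether death is a failure of the rhythm endpoint.
- *The Kaplan-Meier and log-rank analyses contain immortal time.* Statistical methods gives no origin for them. The index clock there is an inference from the visit schedule.

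The 2-year statement can also be read as 2 years from the index procedure, so it is a poor fit rather than a flat contradiction. Leaving detail to a fuller document does not answer the main point, because the article itself fixes the origins by arm.

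**Conclusion.** The point holds for the primary comparison and should be corrected. The origins differ by about 3 months, hybrid has 6 uncounted months from surgery against 3 in control, and the primary assessment falls at about month 27 against 24. These facts follow from the text without any assumption. So does the missing index date for hybrid patients who do not reach catheter ablation, to whom intention-to-treat cannot be applied as written.

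The size is conditional. With no catheter effect, 130 per arm and an assumed month 3–6 hazard 2 to 3 times the later one, the spurious gain is about 3–6 points at 70% control success and 4.5–8 points at 50%. Fisher rejection is then about 7–15% and 10–24%, against about 4% with equal success rates. It would be wrong to say that the design favours hybrid whatever the hazard. It leaves the comparison open to a bias that cannot be separated from a treatment effect.

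**What to change.** For the primary and time-to-event analyses, amend Follow-up, Primary outcome measure and Statistical methods as follows:

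1. Use one origin, randomisation or surgery, for all randomised patients.
2. Set the same endpoint assessment times in both arms, for example 7-day Holters at 3, 6, 12, 18 and 24 months after surgery.
3. Use one common uncounted window, for example counting failures in months 6–24 after surgery in both arms. This covers the blanking after catheter ablation and treats control alike.
4. Keep hybrid patients without catheter ablation in their arm on this clock, and state how they are counted.
5. Count deaths from the same origin in both arms.
6. Keep the index-procedure clock as a sensitivity analysis.

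The Surgical ablation, Catheter ablation and Follow-up sections tie stopping of antiarrhythmics to the first follow-up visit. That wording must be reconciled with the common endpoint clock, so that moving an endpoint assessment does not alter clinical management. The endpoint calendar and the drug-discontinuation visit should be defined separately.

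**Cost.** The change needs an amendment and a shifted hybrid calendar, and is timely because the trial is recruiting. Hybrid now has 6 Holters: one before catheter ablation and five after. The common calendar needs 5, and keeping month 27 for the sensitivity analysis makes 6 again. The price is that control recurrences in months 3–6 leave the primary analysis, and follow-up after catheter ablation is 24 − 3 = 21 months.

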### Interventions

The study consists of two study arms: the *hybrid group*, which will receive surgical CryoMaze followed, in 3 months, by catheter ablation in all patients, or the *surgical CryoMaze group*, in which participants will receive surgical cryoablation with no planned catheter ablation after discharge.

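### As scheduled, the hybrid arm's only early echocardiogram comes after catheter ablation, about 3 months later after surgery than the control arm's, so the change in left atrial dimension is confounded by timing

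*Protocol article*

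**What the plan says.** The last item under Secondary outcome measures in the protocol article is the change in left atrial dimension on echocardiography. The measurement schedule is under Follow-up. It has one early study: "An echocardiogram will be performed within 1 week following the surgical ablation or, if performed, within 1 week after the catheter ablation". Then: "Further echocardiograms will be performed at the 12 and 24 month follow-ups". The same section starts the visit clock at a different procedure in each arm: "surgical ablation in the surgical cryoablation group and catheter ablation in the hybrid group".

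The Interventions section gives the hybrid arm "surgical CryoMaze followed, in 3 months, by catheter ablation in all patients", while control "participants will receive surgical cryoablation with no planned catheter ablation after discharge". The Catheter ablation section repeats the interval: "Patients randomized to the hybrid treatment arm will be admitted for a staged catheter ablation treatment 3 months after the CryoMaze procedure".

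Randomisation follows consent and precedes the operation ("The surgeon will be blinded as to the treatment group until the surgery is completed"), and the Statistical methods section states: "All variables will be analyzed on the basis of the intention-to-treat protocol". The article mentions no pre-operative echocardiogram and does not say which measurement is the reference for the change.

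**The concern.** A between-arm comparison of change needs a reference taken at the same point in both arms and before the treatments diverge. On the natural reading of the schedule, neither condition is met. The control reference is taken days after surgery. The hybrid reference is taken about 3 months later, after the catheter ablation that distinguishes the arms.

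All patients have just had valve or bypass surgery with CryoMaze, so left atrial size may well change in the first postoperative months. That period lies inside the control arm's change and outside the hybrid arm's. A difference between arms could then appear, or a real one be hidden, because of when the echocardiograms were done.

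This is a matter of data collection. If no post-surgery study is done in hybrid patients, no analysis plan can recover it.

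**Working it through.** The plan states no figure for this outcome, so there is none to reproduce. The check is date arithmetic, then algebra, then an illustration on assumed inputs.

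**Step 1. Put both arms on one clock (months since surgery).** Inputs: the 3-month interval from surgery to catheter ablation (Interventions; Catheter ablation), and the arm-specific index procedure and 1-week window (Follow-up). One week is 7/30.44 = 0.23 months.

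| Study | Control | Hybrid |
|---|---|---|
| First | 0 to 0.23 | 3 to 3.23 |
| 12-month follow-up | 12 | 3 + 12 = 15 |
| 24-month follow-up | 24 | 3 + 24 = 27 |

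The first studies are 3 months apart, or between 3 − 0.23 = 2.77 and 3 + 0.23 = 3.23 months allowing for the windows. The later studies are also 3 months apart.

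**Step 2. Expected difference when catheter ablation does nothing.** Let L(t) be mean left atrial size t months after surgery, the same in both arms.

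- Control change: L(24) − L(0)
- Hybrid change: L(27) − L(3)
- Control minus hybrid: [L(3) − L(0)] − [L(27) − L(24)]

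This is zero only if months 0–3 bring the same change as months 24–27.

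**Step 3. An immediate effect of catheter ablation.** Suppose it shifts left atrial size at once by d, and the shift persists. The hybrid change is then [L(27) + d] − [L(3) + d] = L(27) − L(3). The effect d has vanished. Adjusting for the hybrid arm's first study does not repair this, because it would adjust for a value measured after treatment.

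**Step 4. Mixed references within the hybrid arm.** Because the post-catheter study applies only if the ablation is performed, a hybrid patient who never has it would keep a post-surgery reference. Under intention-to-treat, that patient is analysed with hybrid patients whose reference was taken 3 months later.

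**Step 5. Illustration of size.** The document gives no left atrial dimension, SD or expected change. Assume an SD of change of 6 mm and take the 130 per arm from the Sample size calculation section. The standard error of the difference is 6 × √(2/130) = 0.744 mm. The chance of a two-sided P < 0.05 with no true effect, by normal approximation, is:

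| Spurious difference | Difference / SE | Significant in |
|---|---|---|
| 1 mm | 1.34 | 27% |
| 2 mm | 2.69 | 77% |
| 3 mm | 4.03 | 98% |

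A larger SD lowers these percentages and a smaller one raises them. The direction is not known from the document either. A fall in the first 3 months that exceeds any fall over months 24–27 would count against the hybrid arm, and a rise would do the opposite.

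**The case against.** Three objections have force.

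First, the reference is inferred. The article never calls the first echocardiogram a baseline, and a condensed article may leave that to the full protocol or the analysis plan. With a pre-operative reference, the offset would shrink to L(24) − L(27). This stands as a caveat, but the first study is the only early one in the stated schedule.

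Second, the wording could mean a further echocardiogram after catheter ablation, so that every patient also has one after surgery. This is the less natural reading. Even so, the reference would remain unnamed and the final studies would still fall at 24 versus 27 months.

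Third, the outcome is the last of several secondary measures. The primary endpoint is not touched.

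A reader might also infer more than the document supports:

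- **That the bias equals the early postoperative change exactly, whatever catheter ablation does.** By Step 2 this needs no change over months 24–27, and by Step 3 an immediate ablation effect also enters.
- **That the outcome cannot be interpreted at all.** Randomisation precedes surgery, so left atrial size at the final study can be compared between arms without any baseline, subject to the 3-month offset.
- **That the 27%, 77% and 98% are estimates for this trial.** They rest on an assumed SD and assumed differences. The article also names no test for this outcome: its t test is specified for duration of arrhythmia recurrences.

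**Conclusion.** The point holds on the natural reading of the Follow-up section. Echocardiograms fall at about 0, 12 and 24 months after surgery in controls and at about 3, 15 and 27 in the hybrid arm, and the hybrid arm's only early study follows the randomised treatment. If that study is the reference, the between-arm difference in change carries a timing component, [L(3) − L(0)] − [L(27) − L(24)], and loses any immediate effect of catheter ablation.

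The offset of about 3 months follows from the document. Its effect in millimetres cannot be computed from it, and the percentages above show only that a modest shift could matter at this sample size. The conclusion assumes that the early study is one or the other, not both, and that it serves as the reference. It is confined to change in left atrial dimension and is worth correcting while recruitment continues.

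**What to change.** Amend the Follow-up section so that every patient, in both arms, has the first echocardiogram within 1 week after surgery and before any catheter ablation, and name it as the reference for the change. Analyse left atrial size at the final echocardiogram by ANCOVA on that value. If a post-catheter echocardiogram is kept, state that it is not used as a baseline.

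Preferably, time the later echocardiograms from surgery in both arms. Otherwise, report the remaining offset (24 versus 27 months) as a limitation.

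Costs:

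- At most one additional routine echocardiogram per hybrid patient, if the post-catheter one is kept.
- If later studies are timed from surgery, realigned visits. In the hybrid arm, 12 and 24 months after surgery are 12 − 3 = 9 and 24 − 3 = 21 months after catheter ablation, and the hybrid visits are at 3, 6, 12, 18 and 24 months.
- Hybrid patients already past the week after surgery will lack the common baseline. For them, left atrial size at the final visit is compared without it.
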